### Wait-list control group

Children and adolescents in the control group will receive usual care during a 3-month period, which varies between and within regions [22]. During this time, participants will be considered on a waitlist to receive WSTP training and can continue or start any activities provided by therapists or in the community. After completion of T_2_ evaluations, children and adolescents in the control group will complete a target of 12, 45–60 min sessions of the WSTP, delivered by trained personnel as described for the experimental group.

Acknowledging that usual care may include some form of MWC skills training, previous evidence suggests the amount of training received during usual care according to the WSTP will be limited [22, 23].

### Data collection methods

Sociodemographic and wheelchair data (age, gender, diagnosis, previous MWC use, previous MWC skills training, physical activity, MWC size, frame type, wheel size, add-ons) will be collected from the child and parent (or guardian) at baseline (T_1_).

### Primary outcome

MWC skills capacity (i.e., what a person can do in a standardized environment) [32] will be assessed using the WST Version 5.3.1 for MWC users [31]. The child will be asked to execute 30 MWC skills in a standardized environment. Any adverse events during testing will be documented in the WST data collection form by the tester. Participants will be scored on a 4-point scale as Advanced pass (3), Pass (2), Partial pass (1), Fail (0), No part (NP), and Testing error (TE). The total percentage WST score is calculated as: Total percentage WST Capacity Score = sum of individual skill scores / ([# of possible skills – # of NP scores – # of TE scores] × 3) X 100%. As of February 8, 2023, there have been 112 studies indexed in PubMed about the WST (or the questionnaire version [WST-Q]) or that have used these as outcome measures [31]. A minimally clinical important difference (MCID) of 20% relative improvement in WST scores (T_1_ to T_2_) has been suggested for adults [24], but has not yet been determined for children.

### Secondary outcomes

Parent/guardian perception of child’s MWC skills level will be measured using the Wheelchair Skills Level Questionnaire, a screening tool based on the WSP sets of skills [31]. A parent (either mother or father) or guardian will respond to one, two or three questions to determine the skill level: Dependent (0); Indoor (1)—the child is able to use their MWC in the place where they live; Community (2)—the child can independently get their MWC over obstacles in their community; Advanced (3)—the child can use a wheelie to overcome obstacles in their community. If the response to a threshold question is “yes”, the child achieves the level, and the evaluator will ask the question of the next level above. If the answer to the next question is “no”, the child remains in the level below (except if the first question was about advanced skills).

Parent/guardian perception of child’s MWC skills performance (i.e., what their child does in their daily life) [32] and frequency (i.e., how often the child performs the skill) will be assessed using the 30-item Wheelchair Skills Test Questionnaire (WST-Q) Version 5.3.1 for MWC users [31]. A parent (mother or father) or guardian will rate how well and how often their child performs each of the 30 skills on the WST-Q. Assessments with parents/guardians will be done before the child completes the WST to reduce the influence of the objective test. The root performance question asks, “Can your child do (the MWC skill) in their own setting?”. Response options include “yes, very well”, “yes, but not well”, “yes, but with help”, “no” and “no part” with this MWC. For frequency, the root question asks, “How often does your child do (the MWC skill) in their own setting?”. Response options include “always”, “usually”, “rarely”, and “never” and “no part” with this MWC. The total percentage WST-Q scores are calculated in the same way as the WST (defined above). The WST-Q provides an understanding of parent’s perceptions of the change in the child’s skill performance between the baseline and follow-up. The same parent (or guardian) will be asked to complete the questionnaire at T_2_ and T_3_.

MWC use self-efficacy will be evaluated using the Wheelchair Use Confidence Scale for Children using Manual Wheelchairs (WheelCon-M-P), a 33-item self-report scale [33]. Responses are represented through a pictorial Likert type scale with descriptors that range from 0 (pictorial: unhappy face; descriptor: not at all confident) to 4 (pictorial: happy face; descriptor: very confident). Testers will allow the child/adolescent to read through the items on the WheelCon-M-P (the items will be read if needed) and ask the child/adolescent to point to the pictorial that best represents how confident they are that they can do the activity alone and safely. Responses will indicate current level of perceived confidence in 6 areas (i.e., navigate the physical environment in a MWC, perform activities in a MWC, problem solve, advocate for needs, and manage social situations and emotions). Reliability and validity have been documented with previous versions of the WheelCon [22, 34]. The WheelCon-M-P has been validated for use in children and adolescents ages 7–18 years with variable diagnoses (e.g., cerebral palsy, spina bifida) [35].

Satisfaction with participation in meaningful activities will be assessed using the Wheelchair Outcome Measure for Young People (WhOM-YP) [36]. The child/adolescent will create meaningful goals with the tester that require the use of a MWC. The goals may include using their MWC indoor and outdoors at home, at school or in the community. The parent/guardian may be involved in goal setting, but the focus will be on developing goals with the child/adolescent. Ratings of perceived ‘importance’ of the goal (0–10) and ‘satisfaction’ with current performance of this activity (0–10) will be obtained. A mean satisfaction with performance of participation is derived by summing the level of satisfaction for each identified goal and then dividing by the total number of goals. The WhOM-YP has been validated for use in children and adolescents [36].

### Sample size

The sample size was powered to detect a statistically significant difference of 20% between groups [24], using mean change scores from T_1_ to T_2_ in the primary outcome from [name] et al., 2016, which reported a large effect size (Cohen’s d = 1.3) for the WST and a correlation between measures (R^2^) of 0.6 [37]. Based on pilot work, children and adolescents have similar variability in WST capacity scores compared to adults (standard deviation varying from 8 to 20) [26, 27]. However, given the unknown variability associated with age range, a more conservative effect size informed by our pilot work (d = 0.85) and measure correlation (0.60) was chosen. With α = 0.05, and 85% power for between-factors ANCOVA repeated measures design (F-tests) controlling for baseline score (account for function/motor development), a sample size of 18 will be required. Given site variability, each site is powered for primary analysis. G*Power v.3.1.9.2 was used for sample size calculations [38]. Adjusting for a 10% loss to attrition, a total sample size of 60 (20 per site) will be required.

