## Discussion

This paper described the protocol for a randomized wait-list controlled trial to evaluate the effect of the WSTP on MWC skills capacity in children and adolescents, and to explore the influence on MWC use self-efficacy, satisfaction with participation and parents’ perceptions of MWC skills.

Three Canadian sites (Quebec City, Montreal, Halifax) represent major urban centres with access to a large population of children and adolescents who use MWCs. The MWC procurement process in Canada is variable, and there are differences in geography, culture, and climate. In the province of Quebec, MWC are covered by the provincial healthcare system, but services focus mainly on MWC selection and set-up. Observationally, MWCs are replaced about every 5 years, with little follow-up on MWC related services, such as training. However, in Nova Scotia (and other Canadian provinces), wheelchairs are commonly purchased through private insurance, by the family, or obtained through wheelchair recycling programs, with limited access to training, especially for those living in rural areas. This diversity will allow the effectiveness of the WSTP to be evaluated in a variety of clinical contexts and geographical regions, for which site-specific post-hoc exploratory analyses will provide additional insights.

Although an attention-matched control group would provide the most rigorous controlled design, pilot work suggested a high risk of attrition and lack of interest to participate in the study. In fact, parents expressed not wanting to risk their child being allocated to a control group if it meant they would not receive MWC skills training. Given the known benefits of the WSTP in adults [24, 25], strong preliminary evidence in children [26–29], and in effort to mitigate attrition and facilitate recruitment, a wait-list control group was justified for this trial. This design will also reinforce clinical equipoise and reduce the risk of bias associated with lack of equipoise.

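### Eighteen children per site give about 51–56% power at the plan's own d = 0.85, not 85%, so no single site is powered for the primary analysis

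*Protocol article*

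**What the plan says.** All of the calculation is in the Sample size section of the protocol article.

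- The stated target: "The sample size was powered to detect a statistically significant difference of 20% between groups".
- An adult study is cited with d = 1.3 and a correlation between measures written as R² = 0.6. That effect is then set aside: "a more conservative effect size informed by our pilot work (d = 0.85) and measure correlation (0.60) was chosen".
- The test and error rates: "With α = 0.05, and 85% power", for a "between-factors ANCOVA repeated measures design (F-tests) controlling for baseline score".
- The result: "a sample size of 18 will be required".
- The claim about sites: "Given site variability, each site is powered for primary analysis".
- A 10% attrition allowance then gives 20 per site and 60 overall.

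The Analyses section defines the primary comparison as an ANCOVA of T2 WST capacity between the arms, with baseline score as a covariate, and does not split it by site. The Discussion adds that "site-specific post-hoc exploratory analyses will provide additional insights".

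**The concern.** The 18 has to be the total for one site, because 18/0.9 = 20 and 3 × 20 = 60. With 1:1 allocation that is nine children per arm. Nine per arm is very few for 85% power at d = 0.85, even with a useful baseline covariate, so the figure needed checking.

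The claim is also the stated basis for 20 children per site. A reader told that each site has 85% power will treat a site without a significant result as evidence that training does not work there, and the Discussion announces site-level analyses. If the true per-site power is near one half, such a result is expected often by chance alone.

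Three related features of the same paragraph are unclear: whether 0.6 is r or R², how the named test relates to the primary ANCOVA, and what the 20% difference means.

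**Working it through.** **Inputs (Sample size section).** α = 0.05; F-test, hence two-sided for two groups; power 85%; d = 0.85, so f = d/2 = 0.425; correlation 0.60; 1:1 allocation (Design section); N = 18 per site. The number of measurements m entered is not stated, so both m = 2 (T1, T2) and m = 3 (T1 to T3) are tried.

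**1. The named test: repeated measures, between factors.** λ = N f² m / [1 + (m − 1)ρ], with df 1 and N − 2.

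- m = 2: λ = 18 × 0.180625 × 2 / 1.6 = 4.06; power 47.4%; 85% needs N = 42.
- m = 3: λ = 18 × 0.180625 × 3 / 2.2 = 4.43; power 50.7%; 85% needs N = 39 (40 if balanced).

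**2. The primary analysis: ANCOVA at T2.** λ = N (d/2)² / (1 − R²), with df 1 and N − 3.

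| Reading of the inputs | 1 − R² | λ at 18 | Power at 18 | Power at 20 | N for 85% | Power at 54 |
|---|---|---|---|---|---|---|
| 0.60 is r | 0.64 | 5.08 | 55.9% | 61.0% | 34 | 96.9% |
| 0.6 is R² | 0.40 | 8.13 | 76.0% | 80.8% | 23 (24 balanced) | 99.8% |
| d already on the change-score scale, no further gain from baseline | 1 | 3.25 | 39.3% | 43.4% | 52 | 86.5% |

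So 18 is not reproduced by either test at d = 0.85.

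**3. Where 18 does appear.** With the adult effect that was set aside (d = 1.3, f = 0.65), m = 3 and ρ = 0.60, the repeated-measures test gives λ = 18 × 0.4225 × 3 / 2.2 = 10.37 and power 85.6%. At N = 17 power is 83.3%, so 18 is exactly the minimum. This suggests that 18 was carried over from d = 1.3, but that is an inference. With m = 2 the same effect needs 20.

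**4. What 18 can detect.** By ANCOVA at 85% power, d = 1.21 (r = 0.60) or d = 0.96 (R² = 0.6). Pooled, 54 completers detect d = 0.67 (r = 0.60).

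**5. Consequence across sites.** With the same true d = 0.85 at each of three independent sites, the chance that all three are significant is 0.559³ = 17% (r = 0.60), 0.760³ = 44% (R² = 0.6) or 0.393³ = 6% (no gain from baseline). Under every reading, at least one non-significant site is more likely than not.

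**6. The 20% target.** With the cited SD of 8 to 20, d = 0.85 corresponds to 0.85 × 8 = 6.8 up to 0.85 × 20 = 17 WST points. A 20-point difference at d = 0.85 needs an SD of 20/0.85 = 23.5, outside that range. The Primary outcome section gives the 20% as a relative improvement from T1 to T2 suggested for adults, which is not a difference between arms.

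**7. The attrition step** is correct: 18/0.9 = 20 and 54/0.9 = 60.

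**The case against.** The strongest reply is that the shortfall depends on readings the text leaves open.

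- **0.6 as R².** One sentence labels it so. Power at a site is then 76% with 18 analysed and 81% with all 20, a much milder shortfall. This stands as a reason to quote a range, but 85% is still not reached.
- **One-sided test.** The hypothesis is directional, and a one-sided 0.05 test with R² = 0.6 gives 85.9% at N = 18. That competes with d = 1.3 as an explanation of where 18 came from, so the origin cannot be settled. It does not rescue the claim: the section specifies F-tests and states no one-sided test.
- **Other entries.** Entering d as f, or using the within-between interaction with f = d/2, also exceeds 85%. The first misuses the effect size, and the second is not the between-factors test named.
- **18 per arm.** Thirty-six in total gives 87% by ANCOVA, which would suit a whole trial. A site recruits only 20, so the per-site claim still fails.
- **Limited harm.** The primary ANCOVA is not split by site, the Discussion already labels site analyses exploratory, and the pooled sample is ample. This stands as to scope: the primary estimate and the recruitment target are not threatened. It does not make the printed power statement true, and the exploratory label sits badly beside a claim that each site is powered for the primary analysis.
- **The named routine.** The repeated-measures between-factors test averages the arms over all visits, including baseline, whereas the sentence also says that baseline is controlled for. Which routine was run is therefore partly inferred. The ANCOVA result does not depend on it.

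**Conclusion.** The concern holds. At d = 0.85, correlation 0.60 and two-sided α = 0.05, 18 children at a site give 56% power by the primary ANCOVA and 51% by the named repeated-measures test with three measurements (47% with two). Across the other readings of the inputs the ANCOVA figure runs from 39% to 76%. Every two-sided between-group reading with 18 as the site total and d converted correctly falls below 85%. The statement that each site is powered is wrong as written.

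The error is confined to that statement and to the calculation behind it. Pooling the three sites, 54 completers give 97% power by ANCOVA with r = 0.60 (93–95% by the repeated-measures test, and 86% or more by ANCOVA even if baseline adds nothing). These figures assume 1:1 allocation, a common effect across sites and the stated 10% attrition. That 18 came from d = 1.3 is plausible but unproven, and the verdict does not rest on it.

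**What to change.** In the Sample size section, delete the per-site power sentence and replace the calculation with text such as:

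> The primary analysis pools the three sites. A baseline-adjusted ANCOVA at T2 with d = 0.85, r = 0.60, two-sided α = 0.05 and 85% power needs 34 analysed children. Enrolling 60 (54 after 10% attrition) gives 97% power, or 85% power for d = 0.67. Site results are descriptive estimates with 95% confidence intervals.

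State whether 0.6 is r or R². If it is R², the figures become 23 children (24 if balanced) and 99.8% power at 54, and the 85%-power detectable effect must be recalculated. Replace the 20% target with a between-group difference in WST percentage points and the SD assumed, and keep it separate from the adult relative-improvement threshold. Describe the site analyses in the Discussion in the same descriptive terms.

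The cost is one rewritten paragraph and the loss of the per-site power claim. Recruitment stays at 60.

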### Analyses

Summary statistics (mean, median, standard deviation, and percentage) will describe the sample (e.g., sex, gender, diagnoses, previous MWC use, previous MWC training). Assumptions for parametric testing will be verified and data will be screened for outliers [39]. Intention-to-treat analysis will be used, and missing data will be treated using joint modelling multiple imputation methods for repeated methods of longitudinal data [40]. To address the primary objective, T_2_ WST capacity scores will be compared between the experimental and control group using analysis of covariance (ANCOVA or non-parametric equivalent). Covariates will be selected based on influence suggested in the literature (i.e., function/MWC motor development as measured by baseline scores, previous MWC use). Variance (R^2^), statistical significance (95% confidence interval), and effect sizes (partial *n*^2^) will be assessed using Sums of Squares methods. Secondary objectives will be evaluated using linear mixed-effect models, which are flexible to explore within-subject mixed/random effects [34].

Post-hoc exploratory analyses will investigate the influence of age (childhood, adolescence), gender, and MWC experience on effect size and practice dosage using linear mixed-effect models. Comparisons between WST change scores for the experimental group (T_1_-T_2_) and WST changes scores after training in the control group (T_2_-T_3_) will be explored using t-tests. Sensitivity analyses will be conducted on demographic variables (e.g., age, sex, gender) to generate hypothesis and inform future investigation.

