### Procedures

Participants will complete baseline measures (T_1_) and then be assigned to the experimental or control group. The site coordinator will contact the trainer after T_1_ for participants assigned to the intervention group_._ Participants will be asked to attend 12 sessions of the WSTP intervention or continue to receive usual care (3 months), and then complete post-intervention outcomes (T_2_), ideally within a target of one to four days after training. All outcomes will be collected three months after T_2_ to assess retention of skills (T_3_). The site coordinator will schedule all assessments at T_1,_ T_2_ and T_3_ for both groups, as testers will remain blinded to group assignment throughout the study. The site coordinator will call participants 24–48 h in advance of testing and remind the participants about the importance of not revealing to the tester in which group they were assigned. Tester training will include watching an instructional video series (1 h, 37 min total) on how to complete the outcomes and customized in-person or virtual training depending on experience and needs. All data will be stored in a locked channel on Microsoft teams that will be only accessible to testers and the primary investigators. The trial design is depicted in Fig. 1.

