### Intervention (WSTP)

Participants allocated to the experimental group will complete a target of 12, 45–60 min sessions of the WSTP at a target frequency of 1 to 2 sessions per week. The WSTP will be delivered by trained personnel with education or experience in relevant fields (e.g., occupational therapy, physiotherapy, kinesiology, recreation therapy, adapted physical activity). Trainers may have various combinations of clinical practice or research experience with the WSTP. All trainers will complete self-directed WSTP training modules and hands-on practice until readiness to provide training is confirmed by [name], [name] or [name] (each have more than 20 years of experience in training individuals to administer the WSTP).

According to the WSP lesson plan [31], trainers will customize each session based on the age group (child or adolescent) and training goals of each child as determined during baseline testing and in the first training session. Goals can be adapted and modified over the course of the 12 weeks, which may increase motivation and adherence to the training protocol. Subsequent sessions will begin with a 5-min review of progress and socializing, followed by a 10-min warm-up (random practice of the previously learned skills); 20-min of attempting new skills (training on each skill will be carried forward to the next session until the skills are learned or until the trainer and participant mutually agree that training should be abandoned; the trainer will periodically ask the participant to practice newly learned skills to incorporate variability of practice); 10-min cool-down, during which the participant will practice skills in a self-determined manner.

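### The exploratory comparison of training gains between arms uses an unadjusted t-test, which costs some precision and sets scores taken at different times after training against each other

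*Protocol article*

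**What the plan says.** In the Analyses section of the protocol article, the second paragraph opens with "Post-hoc exploratory analyses will investigate the influence of age" and other factors by mixed models. The next sentence sets the experimental arm's WST change from T1 to T2 against the control arm's WST change from T2 to T3, after its own training. These changes "will be explored using t-tests". No covariate or stratification factor is named.

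The primary analysis is handled differently: "T_2_ WST capacity scores will be compared between the experimental and control group using analysis of covariance", with baseline score and previous wheelchair use given as covariates. The Design section stratifies randomisation by site (three) and age group (two).

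On timing, the Procedures section places T2 "ideally within a target of one to four days after training". For T3 it says: "All outcomes will be collected three months after T_2_ to assess retention of skills". The Intervention section sets 12 sessions "at a target frequency of 1 to 2 sessions per week". Under Wait-list control group, controls begin training after T2, following three months of usual care in which other activities may continue or start.

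**The concern.** The two changes are not like for like in three respects.

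- **Precision.** The pre-training score predicts the post-training score and is already recorded. A t-test on raw change does not use it efficiently, and it leaves out the factors on which allocation was stratified.
- **Lag.** The experimental post-training score is tied to the end of training. The control score is tied to the calendar, and the protocol itself describes that visit as a retention assessment. A difference in gains could reflect time since the last session.
- **Start level.** The experimental arm starts from T1, before randomisation. The control arm starts from T2, after usual care and one more WST. Randomisation balances the arms at T1. It does not balance experimental T1 against control T2.

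At stake is how an exploratory result is read: a difference, or the lack of one, could be put down to training when precision, lag or start level explains it.

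**Working it through.** The protocol gives no power or precision figure for this comparison, so there is none to reproduce.

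**Inputs.** From Sample size: correlation 0.60; the adult source's R² of 0.6, which read literally gives r = √0.6 = 0.775; WST standard deviation 8 to 20 points; 10% attrition, so 60 × 0.9 = 54, or 27 per arm. From Procedures and Intervention: the timing rules above. Assumed: equal SD before and after training, and three months taken as about 13 weeks.

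**Step 1, precision.** In units of SD², the residual variance per child is 2(1 − r) for a change score and 1 − r² after adjusting for the pre-training score. The ratio is 2/(1 + r).

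| | r = 0.60 | r = 0.775 |
|---|---|---|
| Change score | 0.80 | 0.451 |
| Adjusted | 0.64 | 0.40 |
| Variance ratio | 1.25 | 1.127 |
| SE ratio | 1.118 | 1.062 |
| 95% CI half-width, change (27 per arm) | 0.488 SD | 0.367 SD |
| 95% CI half-width, adjusted (27 per arm) | 0.437 SD | 0.346 SD |

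At r = 0.60 and SD 8 to 20, the half-widths are 3.9 to 9.8 points (0.488 × 8 and × 20) against 3.5 to 8.7 points (0.437 × 8 and × 20).

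**Step 2, lag.** Twelve sessions take 12/2 = 6 weeks at two per week and 12/1 = 12 weeks at one per week. If control training starts promptly after T2, T3 falls 13 − 6 = 7 weeks to 13 − 12 = 1 week after the last session. A later start shortens this. The experimental target is one to four days.

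**Step 3, start level.** Let δ be the control T2 mean minus the experimental T1 mean, and let training have the same true effect in both arms. Contrasts are experimental minus control.

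- *Model A:* post-training scores in both arms lie on one common line with slope r on the pre-training score. The post-training difference is −rδ. The change contrast is −rδ + δ = (1 − r)δ. The adjusted contrast is −rδ + rδ = 0.
- *Model B:* usual care or retesting moves the whole control arm, the shift persists, and training adds the same gain. The post-training difference is −δ. The change contrast is −δ + δ = 0. The adjusted contrast is −δ + rδ = −(1 − r)δ.

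The documents give no value for δ. For assumed shifts of 5 and 10 points, (1 − r)δ is 0.4 × 5 = 2 and 0.4 × 10 = 4 points at r = 0.60, or about 1.1 and 2.3 points at r = 0.775. The error falls on the change score under A and on the adjusted estimate, with opposite sign, under B. If δ = 0, both are zero.

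Simulation with 27 per arm and r = 0.60 agrees. Under A, shifts of 0.2 and 0.4 SD moved the change contrast by 0.080 and 0.165 SD (expected 0.08 and 0.16), with the adjusted estimate within 0.005 SD of zero. Under B with SD 15, shifts of 5 and 10 points left the change contrast off by about 0.0 and 0.1 points, and the adjusted estimate off by about 2.0 and 4.1 points in size.

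**The case against.** The strongest reply is that this is one sentence about an exploratory analysis. It serves no stated objective, the primary analysis already uses ANCOVA, and the protocol nowhere calls this contrast randomised. All of that stands, and it limits the severity. It is no reason to keep a weaker method when the better one needs no new data.

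A reader might infer that the t-test is biased by some 2 to 4 points and that ANCOVA removes the bias. The documents do not support this. Those figures need an assumed start shift and Model A. Under Model B the same error attaches to ANCOVA. The control start point is post-randomisation, so neither estimator is unbiased by default. The protocol also expects WSTP-type training within usual care to be limited, so the shift may be small.

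A reader might also infer that the analysis is meant to show the training effect repeating in the wait-list arm, or that 25% more variance leaves the trial short of children. The protocol states no such purpose and sets no power target for this comparison.

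On lag, the one-to-four-day figure is a target, both windows are nominally three months, and the Intervention section speaks of training over 12 weeks. At that pace the control lag is about a week or less; seven weeks needs twice-weekly sessions from the start. The trial-design figure, not available in the text reviewed, might show more. So the lag difference can arise under the stated rules but need not be large.

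**Conclusion.** The point holds as a minor one. The unadjusted t-test carries 12.7% to 25% more variance than an analysis adjusted for the pre-training score (standard error 6% to 12% larger). This assumes equal SDs before and after training and a correlation between 0.60 and 0.775. The timing rules allow a control lag of about one to seven weeks against a target of one to four days, narrowing to about a week or less if training fills 12 weeks. Start-level bias is a possibility only: zero without a shift before control T2, and otherwise dependent in size and direction on a model that the trial cannot verify. The primary and secondary analyses are unaffected.

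**What to change.** Reword the sentence in Analyses as follows.

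1. Replace the bare t-test by a linear model of WST change on arm, adjusted for site and age stratum.
2. Beside it, present the model that also adjusts for the pre-training score (T1 in the experimental arm, T2 in controls). Interpret the contrast only where the two agree.
3. Report days from last session to post-training test by arm, with a sensitivity analysis limited to children with similar lags.
4. Describe the result as a non-concurrent, non-randomised exploratory contrast. Neither model removes differences in lag, maturation, number of prior tests or selective attrition.

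The cost is slightly more analysis and a more cautious reading of an exploratory result. WST scores, site and age are already collected. Lag should come from the trainers' detailed logs, provided these record session dates in both arms, which the article does not say outright.
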